### Qualification of participating center

To avoid participant bias while ensuring the sufficient number of cases included to reach our conclusion, all patients were recruited at the same time, and 7 neurosurgical centers were carefully selected considering the following criteria. Firstly, each center covers at least two communities or works as referral units for hemorrhagic stroke. Secondly, the center can carry out various treatment for SSICH, including all varieties of surgery and conservative treatment. Thirdly, the center is capable to admit more than 100 SSICH patients annually. According to an incomplete data, a total of 500 SSICH patients were evaluated across the 7 centers in 2019. Meanwhile, each center can fully represent the level of diagnosis and treatment of SSICH at a national level. Therefore, the centers involved in this study are considered representative.

### Outcomes and study endpoints

All patients will be closely monitored until death or 6 months after the occurrence primary hemorrhage. In this study, the following outcomes will be taken into consideration (Table 3). The primary outcome is the total mortality, including in-hospital and out-of-hospital mortality. The second outcome is the postoperative hemorrhagic complication, and the PIB is our main focus. The functional outcome of patients is another outcome interesting us and will be assessed using modified Rankin scale (mRS). The postoperative adverse cardiovascular/cerebral events (ACCE) include the region of original stroke enlarging, new ischemic stroke occurring outside the operative region, myocardial infarction, repeated revascularization, and deep venous thrombus. The screening, evaluation, and follow-up schedules are detailed in Table 4.

**Table 3 Tab3:** Outcomes to be taken in consideration

(1) Total mortality; (2) postoperative hemorrhagic complication; (3) patients’ functional outcome; (4) postoperative adverse cardiovascular/cerebral events (ACCE).

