## Background

With high mortality and morbidity, spontaneous intracerebral hemorrhage is acute, severe hemorrhagic stroke [1]. For the patients suffering from severe spontaneous intracerebral hemorrhage (SSICH), emergency surgery may provide a means of saving their life [1–7]. Over the past few decades, the morbidity of such ischemia diseases as coronary heart disease has been on the increase with population aging, which may leave nearly a quarter of spontaneous intracerebral hemorrhage patients needing long-term oral antiplatelet treatment (LOAPT) [8]. However, the emergency surgery intended for patients on LOAPT carries a high level of risk to develop intraoperative and postoperative hemorrhagic complications [9, 10]. Up to now, the relative evidences were given only for selective operation, which recommended discontinuation of antiplatelet medications before surgery [1, 9, 11–15], which may hinder emergency surgery for SSICH patients on LOAPT; thus, there was no evidence about the emergency surgery for SSICH patients on LOAPT. Due to the rapid progression of SSICH and the potential risk of newly emerging and re-emerging ischemic events, however, it is usually impossible to discontinue antiplatelet treatment until coagulation function is restored. Once these complications occur, the patients would be faced with an even more catastrophic consequence [16]. Therefore, it is imperative for neurosurgeries and neurologists to develop an appropriate treatment strategy for SSICH patients on LOAPT.

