Meanwhile, it is worth noting that there is still no effective strategy developed to assess the coagulation function of surgical patients on LOAPT. Given antiplatelet medication can have a significant impact on hemostasis and coagulation, the risk of intraoperative hemorrhage and postoperative intracranial bleeding (PIB) is a major focus because they can cause fatality [1, 2]. Though the preoperative screening of coagulation function could be effective in protecting patients from developing hemorrhagic complications, those commonly used methods are not applicable to assess the coagulation function of patients on LOAPT as the antiplatelet medication mainly affects platelet function, rather than clotting factors. Notably, there are various tools, such as thromboelastogram (TEG), reported to aid medical professionals in assessing the platelet function in the cardiac surgery and intracranial traumatic injury [17, 18]. Therefore, they have a potential to assist with the development of suitable treatment strategy for SSICH patients on LOAPT.

In addition to hemorrhagic complications, ischemic complications are also a problem worthy of consideration during the management of SSICH patients on LOAPT due to the hypercoagulable state caused by discontinuing antiplatelet medications. Besides, even though patients are stable after receiving appropriate treatment, it remains debatable to resume antiplatelet treatment. Therefore, there are many SSICH patients who have a history of antiplatelet treatment still stopping antiplatelet treatment after primary hemorrhage, which makes them under high risk of ischemic complications.

According to a previous study, the outcome after spontaneous intracerebral hemorrhage is poor, and the mortality could exceed 30% [1, 19]. Nevertheless, considering a lack of clarity on the effect and safety of emergency surgery for SSICH patients on LOAPT, there is no evidence gathered to support clinical decision-making. Therefore, a prospective cohort study will be conducted to investigate the safety and effect of emergency surgery for SSICH patients on LOAPT, based on which a scientific strategy will be proposed for the selection of an appropriate treatment.

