## Methods

### Study design

Surgical treatment for antiplatelet intracerebral hemorrhage (SAP-ICH) is an ongoing and multicenter study; the flow chart of which is shown in Fig. 1. Beginning in September 2019, this trial is scheduled to be completed by December 2022. Due to unknown and hugely potential intracranial hemorrhage complications after neurosurgery, ethical issues need to be taken into account; therefore, the randomized controlled trial was not suitable currently. The purpose of this study is to evaluate the effect and safety of emergency surgery for SSICH patients on LOAPT, with the focus placed on four aspects: (1) the outcome of operated SSICH patients on LOAPT; (2) the risk of intraoperative and postoperative hemorrhagic complications; (3) the risk of developing postoperative ischemic diseases for SSICH patients on LOAPT; (4) the methods to assess the coagulation state of operated SSICH patients on LOAPT.

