**Fig. 1 Fig1:**
[figure not shown]
Research flow chart

In order to achieve the research objective, it is necessary to recruit all SSICH patients except those not on LOAPT receiving conservative treatment. The inclusion and exclusion criteria are detailed in Tables 1 and 2, respectively. Three cohorts, including two comparative groups and one observational group (Fig. 1), will be established. Firstly, in order to measure the effect of emergency surgery, a comparison will be drawn of the outcomes and complications between SSICH patients on LOAPT receiving emergency surgery and those receiving conservative treatment. Secondly, in order to evaluate the safety of emergency surgery, hemorrhagic complications will be compared between operated SSICH patients who are on LOAPT and those not on LOAPT. Thirdly, the clinical characteristics and coagulation function of SSICH patients on LOAPT will be analyzed to assess the risk of developing ischemic diseases after discontinuing antiplatelet treatment, based on which an effective approach to the assessment of coagulation state will be established for surgery.

**Table 1 Tab1:** Inclusion criteria

Inclusion criteria: (1) 18–75 years old; (2) non-traumatic intracerebral hemorrhage; (3) severe intracerebral hemorrhage, which was defined as patients with supratentorial bleeding volume > 30 ml, infratentorial bleeding volume > 10 ml, midline shift > 1 cm, or large intraventricular hematoma; (4) Glasgow coma score (GCS) < 13; (5) family members agree to provide an informed written consent.

**Table 2 Tab2:** Exclusion criteria

Exclusion criteria: (1) patients had cerebrovascular diseases, e.g., intracranial aneurysm or vascular malformation, and intracranial tumors, which were associated with hemorrhage; (2) hemorrhagic transformation of cerebral infarction; (3) hemorrhage caused by venous thrombosis; (4) patients with severe coagulation disorder, e.g., hemophilia; (5) patients with coagulation dysfunction caused by malignant tumor, hypohepatia, renal dysfunction, thrombocytopenia, coagulation diseases, and so on; (6) patients receiving other anticoagulation medications (vitamin K antagonist and new oral anticoagulants); (7) patients not on LOAPT who receive conservative treatment; (8) the patients who died before or on arriving at the hospital and within a short period (6 h) after admission.	

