### Study definition

After admission, all of the patients would receive standardized care according to the guidelines. Severe spontaneous intracerebral hemorrhage (SSICH) is confirmed by both severe intracerebral hemorrhage radiologically and clinical coma (GCS < 13).

In definition, “on long-term oral antiplatelet therapy (on LOAPT)” refers to patients that received oral antiplatelet treatment on a continued basis for more than 7 days and discontinued antiplatelet medication no more than 7 days after the occurrence of hemorrhage. Antiplatelet therapy involved aspirin, clopidogrel, and dual antiplatelet treatment. Postoperative intracerebral bleeding (PIB) was defined as rehemorrhage within the operative region or new intracerebral hemorrhage associated with the operation on radiological examination.

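### Aim (2) covers intraoperative haemorrhage, but the LOAPT versus non-LOAPT safety outcome is postoperative only, and exclusion (8) drops operated patients who die within 6 h of admission

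*Protocol article*

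**What the plan says.** Three places in the protocol article treat bleeding in theatre as part of the question. The Background says that emergency surgery on LOAPT "carries a high level of risk to develop intraoperative and postoperative hemorrhagic complications", and adds that "the risk of intraoperative hemorrhage and postoperative intracranial bleeding (PIB) is a major focus". Study design makes it part of the second aim: "2) the risk of intraoperative and postoperative hemorrhagic complications".

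The outcome text is narrower. Table 3 lists "1) Total mortality; (2) postoperative hemorrhagic complication; (3) patients’ functional outcome; (4) postoperative adverse cardiovascular/cerebral events (ACCE", and the paragraph above it says: "The second outcome is the postoperative hemorrhagic complication, and the PIB is our main focus". The Results paragraph of the Abstract defines safety in the same way, as postoperative bleeding compared between operated patients on and not on LOAPT. Study definition describes PIB as "rehemorrhage within the operative region or new intracerebral hemorrhage associated with the operation on radiological examination".

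Exclusion (8) in Table 2 removes "the patients who died before or on arriving at the hospital and within a short period (6 h) after admission". It makes no exception for a patient whose operation has already begun.

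**The concern.** An aim that names two kinds of bleeding needs an outcome for each, measured in both groups being compared. Here the operated LOAPT versus non-LOAPT comparison has an outcome for postoperative bleeding only.

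Two further rules act on the most severe cases. The PIB definition depends on a scan, so death before a postoperative scan rules the event out. Exclusion (8) depends on survival after admission. Because the surgery is an emergency, the operation and a fatal bleed could both fall inside the 6 h. Such a patient leaves the safety cohort because of an event that the surgery may have caused. At stake is whether the study can answer aim (2), and whether its safety comparison includes the bleeding that matters most.

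**Working it through.** No stated figure needs reproducing. The check is mainly a reading of the text, followed by an illustration under assumptions.

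**Which bleeding is compared between the operated groups**

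1. Background and aim (2): intraoperative and postoperative bleeding.
2. Study design, text after Fig. 1: the operated comparison is worded as haemorrhagic complications in general, with no time limit.
3. Abstract and Table 3: postoperative bleeding only.
4. Results, statistical paragraph: intraoperative complications appear under the third, observational analysis, which covers patients on LOAPT only.
5. Data collection: intraoperative findings go on the case report form (CRF) for all enrolled patients, so the raw material exists in both operated groups.

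Items 3 and 4 leave no listed outcome for intraoperative bleeding in the LOAPT versus non-LOAPT comparison. Item 2 could be read to allow one, but the more specific statements do not.

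**Where a fatal surgical bleed is counted**

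- Death more than 6 h after admission, with a postoperative scan showing the bleed: can count as PIB and counts in total mortality.
- Death more than 6 h after admission, without a postoperative scan: cannot meet the PIB definition, but counts in total mortality.
- Death within 6 h of admission: the patient is excluded and counts in neither.

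**Illustration of size (assumptions, not figures from the plan)**

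Inputs from Results, sample-size paragraph: PIB 23% on LOAPT and 10% not on LOAPT; 100 and 180 operated patients planned. The paragraph does not say whether these rates include deaths within 6 h, so both cases are shown.

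(a) The 23% leaves such deaths out. Assume k excluded patients beside the 100, all with fatal surgical bleeding. Serious bleeding is (23 + k)/(100 + k):
- k = 2: 25/102 = 24.5%
- k = 5: 28/105 = 26.7%
- k = 10: 33/110 = 30.0%

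(b) The 23% includes them. Assume a fraction x of operated LOAPT patients is lost to early fatal bleeding and none in the other group. The observed rate is (0.23 − x)/(1 − x). Power is for a two-sided 0.05 test of two proportions with pooled variance under the null, at 100 versus 180:
- x = 0: 23%, power 0.82
- x = 1%: 22.2%, power 0.78
- x = 3%: 20.6%, power 0.68
- x = 5%: 18.9%, power 0.56

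**Direction**

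Case (b) assumes that the loss is confined to the LOAPT group. If the same fraction x is lost in both groups, the observed difference is (0.23 − x)/(1 − x) − (0.10 − x)/(1 − x) = 0.13/(1 − x). For x = 1%, 3% and 5% this is 13.1, 13.4 and 13.7 points, against 13 points planned. The difference is then slightly larger, not smaller. Understatement therefore requires a sufficiently greater loss on LOAPT, and the documents give no early deaths by group.

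**The case against.** The strongest reply is that intraoperative bleeding is not ignored. It is recorded on the CRF, complications during surgery are to be investigated in the LOAPT cohort, one sentence words the safety comparison without a time limit, and every enrolled patient's death enters total mortality. This stands. A reader might infer that the worst surgical bleeding is counted nowhere, and the documents do not support that. Only operated patients who die within 6 h of admission are lost entirely.

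A second reply is that the article is condensed and that Fig. 1 and Table 4 are not shown, so a definition of intraoperative bleeding may exist elsewhere. This also stands, and the missing definition is not held against the plan. The mismatch between aim (2) and Table 3 remains, because both are in the text shown.

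A third reply is that the size is unanchored. The documents give no time to surgery, no intraoperative bleeding rate and no count of early deaths. The Discussion names herniation as a main cause of death, so not every early death after surgery is a surgical bleed. This stands too, and the figures above only show how the result depends on the assumption.

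Finally, keeping early operated deaths could distort the comparison of surgery with conservative care. If exclusion (8) were lifted for operated patients alone, operated mortality would move from 30% to (30 + 5)/105 = 33.3% or (30 + 10)/110 = 36.4%, while conservative mortality stayed at 45%. The planned gap of 15 points would shrink to 11.7 or 8.6 through the rule alone. This objection is decisive against a general exception for operated patients. It does not touch an exception confined to the operated safety comparison.

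**Conclusion.** The point holds in a limited form. Aim (2) includes intraoperative haemorrhage, but the listed safety outcome does not, and no comparison of it between the two operated groups is planned. In addition, death before a postoperative scan rules out PIB, and exclusion (8) removes operated patients who die within 6 h of admission. Early fatal surgical bleeding is therefore lost from the safety comparison, while deaths after 6 h still count in total mortality.

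The size of the loss cannot be derived from the documents. A reader might infer that the LOAPT versus non-LOAPT difference must be understated. Given the planning rates of 23% and 10% for PIB, greater early loss on LOAPT is plausible. It is not established, because exclusion (8) applies to every group and equal losses would not shrink the difference. Nor do the documents fix the net bias in the mortality comparison, since early deaths under conservative treatment are removed as well.

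**What to change.** (a) Add intraoperative haemorrhagic complication to Table 3 as a further secondary safety outcome. Derive it from the intraoperative findings already on the CRF, using a definition set in advance, and compare it between operated LOAPT and operated non-LOAPT patients. Keep PIB as the endpoint on which the safety sample size rests. Replacing PIB with a composite would need a planning rate that the protocol does not have.

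(b) For the operated LOAPT versus non-LOAPT safety comparison only, do not apply the 6-h death exclusion in either group once surgery has begun. Report the number of such deaths by group.

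(c) Do not lift exclusion (8) for operated patients alone in the surgery versus conservative mortality comparison. Any change there must apply equally to both arms.

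The cost is protocol wording, one CRF-derived variable and a safety set that differs slightly from the mortality set, which must be stated. Observed complication rates will look slightly less favourable.

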**Table 4 Tab4:**
[figure not shown]
Screen, evaluation, and follow-up schedule

### Study definition

After admission, all of the patients would receive standardized care according to the guidelines. Severe spontaneous intracerebral hemorrhage (SSICH) is confirmed by both severe intracerebral hemorrhage radiologically and clinical coma (GCS < 13).

In definition, “on long-term oral antiplatelet therapy (on LOAPT)” refers to patients that received oral antiplatelet treatment on a continued basis for more than 7 days and discontinued antiplatelet medication no more than 7 days after the occurrence of hemorrhage. Antiplatelet therapy involved aspirin, clopidogrel, and dual antiplatelet treatment. Postoperative intracerebral bleeding (PIB) was defined as rehemorrhage within the operative region or new intracerebral hemorrhage associated with the operation on radiological examination.

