### Thrombelastography (TEG) test and coagulation function assessment system

TEG is performed to monitor the function of platelet with the assistance of Thrombelastograph Coagulation Analyzer (TEG model 5000, Haemoscope Corporation, Niles IL, American). All parameters, including maximum amplitude (MA, mm), citric acid kaolin tracing (CK), reptilase tracing (A), aspirin tracing (AA), and clopidogrel tracing (ADP), are recorded through standard tracing. Based on MA, the rate of platelet inhibition was calculated using the formula as shown below:
$$ AA/ ADP\%=\frac{\mathrm{MA}\left(\mathrm{CK}\right)-\mathrm{MA}\left(\mathrm{A}\mathrm{A}/\mathrm{ADP}\right)}{\Big(\mathrm{MA}\left(\mathrm{CK}\right)-\mathrm{MA}\left(\mathrm{A}\right)} $$

where AA% represents the inhibition to platelet caused by aspirin, and ADP% indicates the inhibition to platelet caused by clopidogrel. Further with traditional coagulation test including bleeding time, prothrombin time, activated partial thromboplastin time, and fibrinogen as well as TEG, we plan to establish a combined coagulation function assessment system in order to assess the surgical risk facing SSICH patients on LOAPT, with the focus placed on PIB. Moreover, for the patients not on LOAPT, it is considered that these patients have normal platelet function and do not need to undergo further relative test.

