## Results

China National Clinical Research Center for Neurological Diseases will be responsible for data analysis. Sample size was calculated by using PASS (Version 15, NCSS corporation, American). All sample size calculations were performed by conducting two-sided test, *α* = 0.05 and *β* = 80% (the degree of control = 80%). In this study, two comparison groups will be established, with the primary and secondary outcomes as the focus in this study. According to our unpublished data collected from 7 participating centers in 2019, for SSICH patients on LOAPT, the total mortality was about 30% for operated patients and 45% for the patients receiving conservative treatment, with the ratio of two groups reaching about 1:1.5. Moreover, for operated SSICH patients, the incidence of PIB was about 23% for patients on LOAPT and 10% for patient not on LOAPT, with the ratio of two groups reaching about 1:2.5. With regard to the primary outcome, our sample size was calculated as 196 (196 SSICH patients on LOAPT, operation group: *n* = 78; conservation group: *n* = 118). As for the secondary outcome, the sample size was 247 (247 operated SSICH patients, LOAPT group: *n* = 70; non-LOAPT group: *n* = 177). Moreover, in order to establish the coagulation function assessment system, the area under curve was expected to be 0.7, and the sample size was set to 92 (92 operated SSICH patients on LOAPT, PIB group: *n* = 23; non-PIB group: *n* = 69). In this case, a minimum of 387 SSICH patients (includes 118 patients on LOAPT receiving conservative treatment, 92 patients on LOAPT receiving emergency surgery, and 177 patients not on LOAPT receiving emergency surgery) may be required in this study to reach our research objective. Thus, to ensure final statistics, a total of 400 patients (patients on LOAPT receiving conservative treatment, *n* = 120; patients on LOAPT receiving emergency surgery, *n* = 100; patients not on LOAPT receiving emergency surgery, *n* = 180; Fig. 1) will be recruited. In this study, 10% of patients would be lost during follow-up. Finally, we decided to recruit 450 appropriate patients.

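### The definition of being on LOAPT limits discontinuation by a date after the haemorrhage and sets no last-dose window before it, so classification is ambiguous and depends on post-onset drug handling.

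*Protocol article*

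**What the plan says.** The Study definition section of the protocol article holds the only definition of being on LOAPT. It has two limbs. The patient must have "received oral antiplatelet treatment on a continued basis for more than 7 days", and must have "discontinued antiplatelet medication no more than 7 days after the occurrence of hemorrhage". No other section states how long before the haemorrhage the last dose may have been.

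The status is then used in four places:

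- **Effect comparison (Study design).** Outcomes are compared "between SSICH patients on LOAPT receiving emergency surgery and those receiving conservative treatment". Here LOAPT is the entry condition for both arms, and the contrast is surgery against conservative care.
- **Safety comparison (Study design).** The plan is that "hemorrhagic complications will be compared between operated SSICH patients who are on LOAPT and those not on LOAPT". Here LOAPT status is itself the contrasted exposure.
- **Eligibility (Table 2, criterion 7).** The study excludes "patients not on LOAPT who receive conservative treatment".
- **Platelet testing (TEG section).** For non-LOAPT patients, "it is considered that these patients have normal platelet function and do not need to undergo further relative test".

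**The concern.** The label is meant to separate patients whose platelets were probably inhibited when they bled from patients whose platelets were not. That requires the time from last dose to bleed. The printed rule instead bounds the stop date on the far side of the bleed.

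Two consequences follow. First, the sentence does not say what to do with a patient who stopped before onset, whether two days or six months earlier, so centres could classify the same patient differently. Second, for a patient taking the drug at onset, status depends on when it is stopped over the following week. That may be after the operation, and the stop date may itself be influenced by surgery or by a postoperative bleed. Exposure status should not be able to depend on an event that can follow the treatment decision or the outcome.

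At stake are the PIB contrast, the make-up of the TEG cohort used to build the coagulation assessment, and who is allowed into the mortality comparison.

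**Working it through.** **Step 1. Apply the sentence to four patients, each with more than 7 days of continuous use.**

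| Patient | Reading (a): stop must fall on days 0 to +7 | Reading (b): any stop up to day +7 |
|---|---|---|
| Taking the drug at onset, stopped on day 0 to +7 | on LOAPT | on LOAPT |
| Stopped a few days before onset | not on LOAPT | on LOAPT |
| Stopped months before onset | not on LOAPT | on LOAPT |
| Taking the drug at onset, still taking it after day 7 | not on LOAPT | not on LOAPT |

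Row 2 is the problem under (a). If operated on, this patient joins the comparator and is not tested by TEG, so the error stays hidden. If treated conservatively, the patient is excluded by criterion 7. Row 3 is the problem under (b), because nothing limits the drug-free gap. Row 4 fails under both: a current user is labelled non-LOAPT. The problems in rows 2 and 3 belong to alternative readings and cannot both arise from one consistent reading.

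**Step 2. Illustrate the effect on the PIB comparison.** The plan gives no figure for misclassification, so there is none to reproduce.

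Inputs from the Results section:
- PIB 23% on LOAPT and 10% not on LOAPT
- "two-sided test, *α* = 0.05 and *β* = 80"% (a power of 80%, printed as beta)
- recruitment targets of 100 operated LOAPT and 180 operated non-LOAPT patients
- calculated secondary sample of 70 and 177

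Assumptions not in the documents:
- a share c of one group is misclassified
- misclassified patients carry the full PIB risk of the group they really belong to

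Power formula, two-sided pooled test of two proportions:

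power = Φ[(|p1 − p2| − 1.96·SE0) / SE1]

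where SE0 = √[p̄(1 − p̄)(1/n1 + 1/n2)], SE1 = √[p1(1 − p1)/n1 + p2(1 − p2)/n2], and p̄ is the weighted mean rate.

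*No misclassification, 100 vs 180.* p̄ = (23 + 18)/280 = 0.1464, SE0 = 0.0441, SE1 = 0.0477. Power = Φ[(0.13 − 0.0864)/0.0477] = Φ(0.914) = 82.0%.

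*Reading (a): share c of the comparator are recent stoppers at 23%.* Comparator rate = 0.10 + 0.13c.

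| c | Comparator rate | Power, 100 vs 180 |
|---|---|---|
| 5% | 10.65% | 77.4% |
| 10% | 11.3% | 72.3% |
| 20% | 12.6% | 61.0% |

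*Reading (b): share c of the LOAPT group are long-stopped patients at 10%.* LOAPT rate = 0.23 − 0.13c.

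| c | LOAPT rate | Power, 100 vs 180 |
|---|---|---|
| 10% | 21.7% | 75.1% |
| 20% | 20.4% | 66.7% |

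Under either reading, c = 10% shrinks the difference from 13 to 11.7 percentage points (23 − 11.3, or 21.7 − 10). At 70 vs 177 the same formula gives 73.7% without misclassification, 63.5% under (a) and 66.4% under (b) at c = 10%. That the starting value is below 80% is a separate matter.

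**The case against.** The strongest reply is that the intended meaning is clear from context. The term says patients are on therapy, taken continuously. The Background describes patients in whom treatment often cannot be stopped until coagulation recovers, and patients who stop after the haemorrhage. The Discussion speaks of stopping for the sake of surgery. All of this points to current users at onset, and the word after may be a slip for before. It is also plausible that status is assigned around admission, since TEG is meant to inform surgical risk. Exclusion criterion 8 removes deaths within 6 hours of admission, which limits the part that very early deaths can play.

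Much of this stands. It makes long-stopped patients in the LOAPT group unlikely in practice, and no section shows that status is assigned after outcomes are known or that patients stay on the drug beyond day 7. But it does not repair the sentence. It gives no rule for a patient who stopped shortly before onset, and nothing in the article says that the wording is a slip.

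Three stronger readings are tempting and are not supported:

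- A reader might infer that LOAPT is the exposure in both comparisons. It is the exposure only in the PIB comparison.
- A reader might add the two power losses together. They come from mutually exclusive readings.
- A reader might take the losses as estimates of harm. The shares and the risks given to misclassified patients have no source in the document, and at a 5% share under reading (a) the loss is under 5 percentage points.

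**Conclusion.** The wording defect is real and follows from the text alone. The sole definition bounds discontinuation after onset, leaves the interval before onset unstated, and literally rejects a patient still on the drug after day 7. Followed as printed, it can put patients in the wrong group for the PIB comparison and the TEG cohort, and wrongly exclude conservatively treated patients through criterion 7. For the mortality comparison it affects who enters, not the surgery contrast, and no size can be put on that.

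The size for PIB is illustrative only: from 82% power to 72% under reading (a), or to 75% under reading (b), at an assumed 10% share with 100 vs 180 patients. If misclassified patients do carry the risk of their true group, the bias shrinks the PIB difference and makes surgery on LOAPT look safer relative to the comparator. The article does not show how many patients are affected or whether centres applied the literal wording.

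**What to change.** Replace the definition with one that uses only drug history known at haemorrhage onset: continuous oral antiplatelet use for more than 7 days, with the last dose within a stated window before the bleed. The sponsor should confirm the length of that window; none is proposed here.

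Record discontinuation or resumption after onset as a separate follow-up variable. The third objective, on ischaemic events after stopping, needs it in that form anyway.

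Re-check the classification of patients already enrolled against the corrected rule where last-dose information is available, and report how many change group or cannot be classified.

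The cost is a one-sentence amendment and a review of last-dose information. The data collection text does not list last-dose dates explicitly and the schedule in Table 4 is not visible in the copy reviewed, so some dates may have to be retrieved from hospital records. No new patient procedure is required by the wording change itself.
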